#### Sexual Agreements

Separately tabulated data about disclosure of sex outside the relationship and percentage of couples with agreements involving sex outside the primary relationship will be developed. These analyses will be descriptive and include analyses stratified by race/ethnicity, study arm, and couple serostatus. These analyses will also characterize the prevalence of agreements about sex outside relationships, the extent to which those agreements are adhered, and any shift of adopting safer sexual behaviors with outside partners, again stratified by race/ethnicity and study arm. A focus of the analysis will be identifying differences across the study arms in the percentages of couples who report a shift to safer sexual agreements at follow-up. In addition, the Actor-Partner Interdependence Model (APIM), which uses the dyad (eg, couple) as the unit of analysis, will be used to predict how an individual and his partner’s reports of dyadic characteristics—described within Lewis’ model [44]—affect whether the individual formed, changed, and kept the sexual agreement he had with his main partner [31]. Procedures for using SAS to calculate actor-partner effects with dichotomous outcomes with male couples (eg, indistinguishable dyads) have previously been reported in detail [31] and will be used for the proposed RCT.

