### Preliminary Data

An online survey of 1285 MSM from across the United States was conducted to examine willingness to use the proposed intervention (unpublished data). Respondents were recruited through targeted advertisements on Facebook over 10 days from October to November 2012. Of the 907 men who self-reported a negative HIV serostatus and provided complete data, 72.0% (653/907) reported they would be likely to use a home-based HIV test, 69.0% (626/907) reported they would be likely to use CHTC, and 75.0% (680/907) reported that they would be likely to use a home-based HIV test together with a VSee video-based CHTC session. The willingness to use the proposed intervention did not vary by age (*P*=.60), race (*P*=.91), recent (ie, <12 months) HIV testing behavior (*P*=.43), or recent CAI (*P*=.39). Among those with main partners (510/907, 56.2%), 82.0% (418/510) reported they would likely use the intervention. Among those who reported recent physical violence from an intimate partner (55/502, 11.0%), 67% (37/55) reported they would likely use the intervention. Emory University Center for AIDS Research also funded a trial of Skype-based counseling with 15 male couples from Atlanta to examine feasibility and acceptability of the video-chat counseling session. Although the trial did not incorporate HIV testing, 15 male couples were recruited using the same online recruitment methods as proposed in this intervention. Couples completed a baseline survey describing recent sexual risks and sexual agreements in their relationships; then each couple underwent an approximately 45-minute counseling session via Skype video-based chat. During the session, the Emory-based counselor talked to the couple about their sexual agreements and their management of HIV risks, and then referred them to local services. Approximately half of the couples were in monogamous relationships; the mean relationship duration was 17 months. A total of 10 couples had formalized agreements around sex outside of the relationship, which ranged from monogamy to allowing sex with outside partners under certain conditions. Couples then completed an online survey about their experiences with the Skype video-based counseling session. Satisfaction was universally high—mean satisfaction was 4.8 out of 5 and 100% of participants said they would recommend the service to other male couples. Crucially, 100% of couples stated that they would be willing to include HIV testing in the video-based counseling session, with the main reasons being “convenience” and “having access to counseling while testing at home.”

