#### Sexual Agreements

All surveys include questions taken from previous studies of male couples’ sexual agreements [45]. Participants are asked which of the following best describes their current sexual agreement with their main partner: “neither of us can have sex with outside partners,” “we can have sex with outside partners, without any conditions or restrictions,” “we can have sex with outside partners, but with conditions or restrictions,” or “we do not have an agreement.” Additional items about agreements will further assess whether couples permit (or do not permit) that certain sexual behaviors, mainly CAI and oral sex, can occur with outside partners. In follow-up surveys, participants are asked whether their agreement had been broken in the previous 3 months, if they disclosed the agreement breakage to their partner, whether they have changed their agreement, and, if relevant, how their agreement had changed.

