### Sample Size

The goal is to enroll and maintain a sample of 400 male couples: 200 serodiscordant and 200 seroconcordant couples, 100 of each couple per arm (experimental vs control). To achieve this, the intervention aims to screen approximately 1000 male couples—500 serodiscordant and 500 seroconcordant male couples—and will exclude those with a recent (<12 months) history of IPV. Assuming 15% of male couples have a recent history of IPV, this will produce approximately 850 couples for randomization, 425 per arm. Allowing for 20% loss to follow-up and additional 20% relationship dissolution, this will produce a sample of 400 male couples who are expected to complete the prospective RCT. The sample size is calculated based on the detection of significant changes in each of the main outcomes (ie, changes in sexual risk-taking, such as CAI), formation and adherence to explicit sexual agreements, and relationship functioning for the management of HIV risk. As an example, we will assume that about 25% of male couples change agreement status after couples counseling and we will use a two-sample test of binomial proportions with type I error rate at 5%. Using these assumptions, it is determined that 52%, 67%, and 85% statistical power is necessary to detect a difference of 10%, 12%, and 15%, respectively, in a change-of-agreement status between the two arms within seroconcordant or serodiscordant groups (ie, comparing 150 male couples per arm). In other words, under the same conditions, the probability is .52, .67, and .85 that the lower bound of the confidence interval for the proportion change in agreement status in the intervention arm is at least 3%, 5%, and 8% different than the proportion in the control arm, respectively, when the alternative hypothesis is true. If data is pooled across seroconcordant and serodiscordant couples, assuming that combining data makes sense in terms of the magnitude and direction of the intervention effect, then 81%, 92%, and 99% statistical power is necessary to observe differences of 10%, 12%, and 15%, respectively (ie, comparing 300 male couples per arm). In this case, at least 80% statistical power will be necessary to detect as little as a 5% difference between the lower bound of the confidence interval for the proportion in the intervention versus the control arm. Based on discussions with participant advocates and partnered community-based organizations, it is projected that any difference exceeding 5% would be scientifically meaningful and would have public health impact. The analysis also considers differences in linkage to HIV care among HIV-positive individuals in each arm, but it is not powered to detect significant differences, given the small number of incident positive cases.

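### The focal comparison of couples shifting to a safer sexual agreement names no adjustment for baseline agreement type, which is collected and could add precision; the size of the gain depends on figures the article does not give

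*Protocol article*

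**What the plan says.** The protocol article (Primary Outcomes) lists sexual agreements among the primary outcomes. Its measurement section applies to all surveys, including baseline: "Participants are asked which of the following best describes their current sexual agreement with their main partner", with four response categories running from no outside partners to no agreement.

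Under Statistical Analysis, the Sexual Agreements subsection calls the agreement tabulations descriptive. They are stratified by race/ethnicity, arm and couple serostatus. It then makes a focus of "identifying differences across the study arms in the percentages of couples who report a shift to safer sexual agreements at follow-up". No test, model or covariate is named in that sentence.

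Tests for percentages of this kind appear in two other places:
- Sample Size uses a "two-sample test of binomial proportions with type I error rate at 5" per cent.
- The Sexual Risk-Taking subsection compares outcome prevalence between arms by chi-square or Fisher's exact test. The baseline covariates listed there are race, age and relationship duration.

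Randomization is stratified on serostatus only. Models are also named. The analysis Overview gives regression, mixed models and GEE for longitudinal items and scales. The Sexual Agreements subsection adds an actor-partner model whose stated predictors are the partners' dyadic characteristics.

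**The concern.** A shift is defined relative to where the couple started. A couple whose baseline agreement excludes all outside partners is already at the restrictive end of the four-category item. A couple with an open agreement, or with none, has somewhere safer to go. A raw comparison of percentages puts both kinds of couple into one binomial variance. If baseline type predicts the event strongly, the confidence interval for a primary outcome is wider than the collected data require.

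The article names the comparison, the descriptive strata and some covariates, and the variable that marks the starting point of the shift is in none of them. As described, the actor-partner model does not fill the gap, because study arm is not among its stated predictors.

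**Working it through.** **Inputs from the article (Sample Size, Preliminary Data)**
- Rate: "we will assume that about 25% of male couples change agreement status after couples counseling". This is any change of status, not a shift to safer, so applying it to the focal outcome is an assumption.
- Planned size: 100 couples per arm in each serostatus group, so 200 per arm pooled.
- Share already monogamous: "Approximately half of the couples were in monogamous relationships", from a pilot of 15 couples, of whom 10 had formalized agreements.

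**Inputs assumed:** the share m of trial couples that start monogamous, and their event rate.

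**Reproducing the plan's power.** The article states "52%, 67%, and 85% statistical power is necessary to detect a difference of 10%, 12%, and 15%, respectively" ("ie, comparing 150 male couples per arm"), and 81%, 92% and 99% at 300 per arm. A two-sided 5% two-proportion test without covariates, with rates centred on 25% (20 v 30, 19 v 31, 17.5 v 32.5), gives 51.6%, 67.2% and 85.5% at 150 per arm and 80.9%, 92.6% and 99.0% at 300. The stated power therefore rests on the unadjusted test. The 150 and 300 used there differ from the planned 100 and 200; that is a separate matter, and the figures below use the planned numbers.

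**Unadjusted, 200 per arm, 10 points.** Variance = [p0(1−p0) + p1(1−p1)]/n = (0.16 + 0.21)/200 = 0.00185, so SE = 0.0430. Power = Φ(0.10/0.0430 − 1.96) = 64%.

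**Stratified, no events among monogamous couples.** With q = p/(1−m), variance = (1−m)²[q0(1−q0) + q1(1−q1)]/[n(1−m)]. At m = 0.5, q is 0.40 v 0.60, so variance = 0.25 × (0.24 + 0.24)/100 = 0.0012, SE = 0.0346 and power = 82%. The variance falls by 1 − 0.0012/0.00185 = 35%.

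| m | Unadjusted | Stratified | Gain (points) |
|---|---|---|---|
| 0.2 | 64% | 68% | about 4 |
| 0.3 | 64% | 71% | about 7 |
| 0.4 | 64% | 76% | about 11 |
| 0.5 | 64% | 82% | about 18 |

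A version with pooled null variance gives gains of 3.8, 6.8, 11.1 and 17.5. A simulated Cochran-Mantel-Haenszel test at m = 0.5 (20,000 runs) gave 63.6% unadjusted and 80.7% stratified. For a 15-point difference at m = 0.5 the gain is only 5.5 points (93.7% to 99.2%), because power is already high.

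**Monogamous couples can also have the event** (m = 0.5, simulated, 200 per arm; control v intervention rates):
- Monogamous 5% v 10%, others 35% v 50%: 64.2% to 72.0%, about +8.
- Monogamous 10% v 20%, others 30% v 40%: 64.5% to 66.5%, about +2.
- At the edges: 15% v 25% with 25% v 35% gives almost nothing (63.9% to 64.3%). 5% in both arms with 35% v 55% gives about +10 (63.8% to 73.9%).

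**Type I error.** Simulated at 0.053 for both the raw and the stratified test.

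**The case against.** The strongest reply is that the article never says the comparison is unadjusted. The two-sample test belongs to a sample-size illustration, the chi-square and Fisher tests stand under risk-taking, and the Overview names regression and GEE for longitudinal items, of which agreement type could be one. Covariates may also sit in an analysis plan that is not shown. This stands in part: the unadjusted reading is an inference. But no model in the article is tied to the shift percentage, and baseline agreement type is absent from every list of strata and covariates it does give.

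Three stronger readings are tempting, and the document does not support them.
- A reader might infer that the trial gives up 18 points of power. That is one scenario: half of couples monogamous, none able to have the event, and a rate for any change of status applied to a shift to safer. In the pilot only 10 of 15 couples had formalized agreements. If the other 5 were all among the roughly 7 or 8 monogamous couples, only 2 or 3 of 15 (13% to 20%) had a monogamy agreement.
- A reader might infer that monogamous couples cannot shift at all. What counts as safer is not defined. For serodiscordant couples, condomless sex with the main partner is itself at-risk sex, so a safer agreement within the couple is conceivable, although the four-category item concerns outside partners only.
- A reader might infer that chance imbalance in baseline type biases the result. Its SD at m = 0.5 is √(2 × 0.25/200) × 0.5 = 0.025. But 0.00185 − 0.025² = 0.001225, which is about the stratified variance. This is the same efficiency loss restated, not a further problem.

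**Conclusion.** The point holds as a conditional matter of precision. The direction is clear: a prognostic baseline variable that is already collected is not named for the comparison the article calls a focus. The size is not known. At 200 per arm and a 10-point difference centred on 25%, the gain over 64% power is about 4 to 18 points for a monogamous share of 20% to 50% with no events in that group. It is about 2 to 8 points if those couples can also have the event, and close to none if baseline type is only weakly prognostic. Both the share and the event rate are assumptions, since the only related figure is the 15-couple pilot. The raw comparison remains valid: unbiased under randomisation, with correct type I error.

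**What to change.** Make the primary arm comparison of this outcome a Mantel-Haenszel stratified risk difference, or a logistic regression standardised to a risk difference, with a 95% confidence interval. Adjust for couple-level baseline agreement type and randomisation serostatus. Either method keeps the percentage-point scale used in Sample Size. Keep the raw percentages by arm as description.

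Apply it to all couples with follow-up agreement data. It should not be presented as keeping every randomised couple, because the article itself allows for 20% loss to follow-up and a further 20% relationship dissolution.

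The cost is a few lines of analysis wording and one model on data already collected. The small downside is that a coding rule is needed, fixed before unblinded data are seen, for couples whose partners report different baseline agreements. If many couples are discrepant, the coded variable will predict less well and the gain will shrink.

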#### Linkage to Care

The percentage of HIV-positive respondents who receive a timely (<3 months) comprehensive visit—a visit including a CD4 count, viral load count, and the date of their first care visit—will be tested for significance across the two study arms. The percentages of couples who are seroconcordant negative, seroconcordant positive, and serodiscordant, as part of the description of the analysis samples, will be recorded. To assess whether the concordancy of the couple modifies the intervention effects, formal statistical tests—likelihood ratio tests in mixed models and generalized score tests in marginal models—of the null hypothesis will be conducted. The null hypothesis is that the two-way interaction effect for the aforementioned items and scales between intervention and concordancy is zero. If the statistical test does not reject the null hypothesis, the concordancy main effect in the model will be retained, removing the two-way interaction, and conclude that there is not sufficient evidence to suggest that concordancy modifies the intervention effect.

The safety of the intervention at both the individual and couple levels will be evaluated by examining reported IPV within the relationship and relationship dissolution. At the individual level, prevalence of each individual adverse outcome or any adverse outcome will be calculated. Prevalence of outcomes will be compared across the control and intervention arms, by serostatus of the couple, and by relationship duration using chi-square tests or Fisher’s exact tests, as appropriate. At the couple level, the APIM will be used to predict how an individual and his partner’s reports of dyadic characteristics affect the individual’s experience of IPV and reported relationship dissolution.

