A vital cornerstone to prevention and linkage to care is HIV testing [43]. This paper describes the protocol for a new randomized controlled trial (RCT) that combines the CDC-recommended prevention strategy of CHTC with home-based testing for male couples via video-based counseling and testing. By using video-based technologies (eg, VSee video chat), male couples receive counseling and support from a remote online counselor, while testing for HIV at home. This combination of HIV testing efforts is needed and timely because few interventions exist for male couples, especially those who live in rural areas and areas with few LGBTQ resources. This RCT aims to examine and compare the intervention’s effects on the relationship’s ability to manage HIV risk, formation and adherence to explicit sexual agreements, and sexual risk-taking between self-reported concordant-negative and self-reported discordant male couples. Participants complete surveys at baseline, 3 months, and 6 months. It is hypothesized that couples exposed to the intervention will learn communication skills and receive psychoeducation that allows them to work together on HIV prevention planning. As a result, it is hypothesized that couples exposed to the intervention will be more likely to report discussing and forming sexual agreements and be more likely to adhere to agreements, yet also more likely to disclose if they break their agreements.

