#### Sexual Risk-Taking

The definition of at-risk sex will be serostatus specific. For serodiscordant couples, at-risk sex will be CAI with either their main or outside partners. For seroconcordant-negative and seroconcordant-positive couples, at-risk sex will be CAI with outside sex partners. While data on PrEP use and adherence will be collected, the definition of at-risk sex focuses on condom use given the CDC recommendation for continued condom use for those adopting PrEP. The incidence of at-risk sex acts will be calculated as an incidence density, with the numerator being the number of individual at-risk sex acts and the denominator being person-years of follow-up time. Comparisons of the incidence of at-risk sex acts will be made by comparing incidence densities between the two arms. Incidence rates per couple-year of follow-up will be estimated and compared using exact methods based on the Poisson distribution by using the GEE approach. Baseline covariates include race, age, and duration of relationship. Period incidence rates—6-monthly incidence density rates—of at-risk sex will be estimated by performing a GEE Poisson regression analysis of the 6-monthly counts. This will be implemented using the PROC GENMOD procedure by SAS (SAS Institute Inc) [56] and using an exchangeable correlation structure for the repeated observations of couples. The incidence density ratio, or incidence rate ratio (IRR), is the ratio of the incidence density in one treatment group (intervention arm) to that of another group (control arm). Results by each baseline covariate will be summarized as the IRR and the 95% confidence interval. These analyses will be descriptive and include analyses stratified by race/ethnicity. Prevalence of each outcome will be calculated and prevalence of outcomes will be compared in the control and intervention groups using chi-square tests or Fisher’s exact tests, as appropriate.

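### The arm-by-serostatus interaction is dropped from the item and scale models whenever its test is non-significant, which can leave a stated comparison without an estimate or interval

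*Protocol article*

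**What the plan says.** The Introduction sets out to compare the intervention's effects on managing HIV risk, on sexual agreements and on "sexual risk-taking between self-reported concordant-negative and self-reported discordant male couples". Randomization is 1:1 and stratified on the two serostatus levels. Sample Size sets a goal of 200 couples of each kind, 100 per arm.

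Effect modification is dealt with in a paragraph under Linkage to Care, but it reaches back beyond that outcome: "The null hypothesis is that the two-way interaction effect for the aforementioned items and scales between intervention and concordancy is zero". The test is a likelihood ratio test in mixed models or a generalized score test in marginal models. The rule that follows is: "If the statistical test does not reject the null hypothesis, the concordancy main effect in the model will be retained, removing the two-way interaction". The plan would then conclude that there is too little evidence that concordancy modifies the effect.

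Sample Size gives power for the arm difference within a stratum (150 couples per arm) and pooled (300 per arm). It gives none for the interaction. It makes pooling conditional on the effects being compatible in size and direction.

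**The concern.** The comparison between concordant-negative and discordant couples is an aim of the trial, and the stratified allocation and equal strata serve it. Under the rule, a significance test decides whether the model still contains that comparison. If the test does not reject, the fitted model has a serostatus main effect and one arm effect. It then holds no estimate of how far the arm effects differ and no interval to show what differences remain plausible.

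Failure to reject is weak support for a common effect unless the test had good power against differences that matter. At stake is that the common effect is read as applying to both kinds of couple, and that readers cannot see how uncertain the contrast is.

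**Working it through.** **1. Which models the rule governs.** It refers back to items and scales. The Overview of Statistical Analysis: Dyadic Characteristics describes longitudinal models for item and scale measures, with likelihood-based inference for mixed models and generalized score and Wald tests for marginal models. The rule names the same two model families and matching tests, so those models are its most natural target. The article gives no SD or correlation for any scale, so power for the scales cannot be calculated. The only outcome with usable inputs is change of agreement status, taken here as an illustration.

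**2. Inputs (Sample Size).** The rate is 25%: "we will assume that about 25% of male couples change agreement status after couples counseling". The type I error is 5%, taken as two-sided because that reproduces the stated power. Couples per arm per stratum are 100 (the stated goal) or 150 (used for the power figures); both are carried.

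**3. Reproducing the stated power.** Take 25% as the average of the two arms. Then SE = √(2 × 0.25 × 0.75 / n) and power = Φ(d/SE − 1.96).
- n = 150: SE = 0.0500; for d = 10, 12, 15 points, power is 51.6%, 67.0%, 85.1% (stated 52%, 67%, 85%).
- n = 300: SE = 0.0354; power is 80.7%, 92.4%, 98.9% (stated 81%, 92%, 99%).

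**4. Power for the interaction.** The interaction is the difference between two risk differences, so four cells contribute: SE = √(4 × 0.25 × 0.75 / n). Power = Φ(δ/SE − 1.96) + Φ(−δ/SE − 1.96), where δ is the between-stratum difference in arm effect.

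| Couples per cell | SE | δ = 10 | δ = 15 | δ = 20 | δ for 80% power |
|---|---|---|---|---|---|
| 100 | 0.0866 | 21.1% | 41.0% | 63.7% | 24.3 points |
| 150 | 0.0707 | 29.3% | 56.4% | 80.7% | 19.8 points |

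The last column is (1.960 + 0.842) × SE. The interaction would be removed in the complementary share of trials: 79%, 59% and 36% at 100 per cell; 71%, 44% and 19% at 150.

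**5. Sensitivity to how the 25% is placed.** Suppose three cells are at 25% and the effect falls in one cell only. Across a rise or a fall from 25%, and across the risk-difference and log-odds scales, power at 100 per cell runs over 19–26% (10 points), 34–56% (15) and 52–86% (20). At 150 per cell it runs over 26–36%, 47–73% and 69–96%.

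**6. What the common effect would show.** If the effect is 15 points in one stratum and nil in the other, equal strata give a common effect centred on (15 + 0)/2 = 7.5 points, which is 7.5 points away from the truth in each stratum.

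**7. What the intervals would show.** The 95% half-width for the interaction is 1.96 × 0.0866 = 17.0 points at 100 per cell and 1.96 × 0.0707 = 13.9 at 150. For a stratum-specific effect it is 1.96 × √(2 × 0.25 × 0.75 / n) = 12.0 and 9.8 points.

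**The case against.** The strongest reply is that the plan does answer the question. It tests the interaction formally, and its conclusion is properly worded: it speaks of insufficient evidence and does not claim that the effects are equal. The Introduction states no hypothesis about serostatus differences. A condensed article may also leave table content to a fuller document. The wording of the conclusion does stand as proper. But the article does not leave the matter open: it states a data-driven choice of model, and a test result alone does not give the size of the contrast.

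A reader might infer more than the article supports, in four ways.

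- *That no stratum-specific result survives anywhere.* This is not so. The Overview analyses dyadic characteristics by HIV status and arm, Sexual Agreements plans tables by arm and couple serostatus (called descriptive), and Sample Size implies arm comparisons within each serostatus group. None of these is described as giving the between-stratum contrast with an interval.
- *That the comparison is lost in most trials whatever the true difference.* In the illustration this holds at 10 points for both cell sizes, but at 15 points only with 100 per cell, and at 20 points with neither.
- *That the test is shown to be weak for the scales.* Both partners report them at several time points, so power may differ, and the article gives nothing to compute it from.
- *That the rule causes two at-risk-sex definitions to be mixed.* Sexual Risk-Taking says "The definition of at-risk sex will be serostatus specific" and compares incidence between arms in its own Poisson analysis, with no interaction step. Any mixing arises there, not from this rule.

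**Conclusion.** The point holds for the item and scale models that the rule governs. When the interaction test is non-significant, those models give one common arm effect and no interval for a comparison that the Introduction names as an aim. On the article's only quantified example, that would happen often for differences of 10 to 15 points: about 59–79% of trials with 100 couples per cell and 44–71% with 150.

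These figures rest on a binary couple-level outcome near 25%, a two-sided 5% test, a normal approximation and no loss of couples. They illustrate the rule and are not a power statement for the scales. Whether the rule also extends to agreement change or at-risk sex is not clear from its wording. The difference between 100 and 150 couples per arm per stratum in Sample Size is a separate matter; the conclusion does not depend on which applies.

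**What to change.** Replace the removal rule with a statement that the interaction test does not choose the model. For each outcome the rule covers, always report the arm effect within each serostatus stratum and the interaction estimate, each with a 95% CI, and give the pooled stratum-adjusted arm effect alongside. The test and the present cautious conclusion can stay. The sentence should also name the outcomes covered, since the present reference back is loose.

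The cost is a sentence or two and a few more table rows, with no new data and no change to the design. The downside is small: stratum estimates are less precise than the pooled one (in the illustration about ±12 points at 100 per cell or ±10 at 150), but those intervals show how much the trial can say about each kind of couple.
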